### Ethics and dissemination

#### Protocol amendments

Protocol amendments will be documented with a brief description of the change and reference (date and number) when changes in the existing protocol significantly affect the safety of subjects, the scope of the investigation, or the scientific quality of the study. The coordinating investigator is obligated to notify this protocol amendments to all the investigators and the reviewing IRB and other relevant parties as appropriate.

#### Consent or assent

The clinical investigator ensures that informed consent is obtained from each research subject before that subject participates in the research study. When the research subject is disabled to consent for critical illness, informed consent is obtained from the authorized surrogates, for which the prior approval from the IRB is a prerequisite. We will only obtain consent to use data and samples for the research question described in this protocol. Thus, we do not intend to use participant data or biological samples in ancillary studies.

#### Access to data

Data from the VIP study will be made available in the future for collaborative research questions. Such requests must be authorized by the principal investigators and the appropriate Human Research Ethics Committees and Human Research Governance Safety Entities.

#### Ancillary and post-trial care

All patients would be treated, monitored, and routinely assessed regarding the VAP development and recovery process in each participating study center in China.

#### Dissemination policy

The findings from the data analysis will be disseminated in various ways, including abstracts, posters and presentations at conferences, and published manuscripts in peer-reviewed journals. These will also be reported to national, provincial, and local governments to inform policy and reports to funding bodies, institutes, and hospitals that participated in and supported the cohort study. Members of the study team will have publishing and authorship rights following the International Committee of Medical Journal Editors requirements for authorship and as described in research agreements.

### Statistical analysis

#### Sample size estimation

Zhang et al. reported the incidence of 33.7% in a meta-analysis and systematic review of 334 publications concerning ICU-acquired pneumonia and VAP in China [1]. According to a meta-analysis by Ouyang et al. [28], a treatment effect with a relative risk reduction (RRR) of 51.4% is observed in ICU patients receiving postpyloric tube feeding (PTF) compared with receiving gastric tube feeding (GTF). A 10% inferiority margin is predetermined following previous guidelines and reviews. We calculate that enrollment of 924 participants will have a power of 80% to detect an absolute reduction of 17.3% (relative risk reduction of 51.4%) in the study group compared to 33.7% of the control group, allowing a loss of follow-up or withdrawal of 10%. Considering the prevalence of VAP in our patients and assuming the rate of patient recruitment of about ten per month per center (with three participating centers), this trial will be finished within 3 years.

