## Methods/design

### Study design

The VIP study is designed as a prospective, multicenter, open-label, randomized, parallel-group, GTF-controlled (PTF vs. GTF 1:1) superiority trial in 4 tertiary care hospitals. The participating sites in this study include medical/surgical, medical, surgical, or emergency ICUs (see Table 1 for details of participating centers). Patient enrollment is expected to last for up to 36 months. The end of the study is defined as the last follow-up of the last enrolled patient. The trial has been registered at chictr.org.cn (ChiCTR2100051593). We used the Standard Protocol Items: Recommendations for International Trials (SPIRIT) reporting guidelines [29], and the SPIRIT checklist is attached in the Supplementary appendixes.

**Table 1 Tab1:** Research settings and names of each ethics committee

Research setting	Ethics committee name	Hospital rank and location
Maoming People’s Hospital	Medical Ethics Committee of Maoming People’s Hospital	Tertiary, Maoming, Guangdong, China
Guangdong Provincial People’s Hospital	Medical Ethics Committee of Guangdong Provincial People’s Hospital	Tertiary, Guangzhou, Guangdong, China
General Hospital of Southern Theater Command	Medical Ethics Committee of General Hospital of Southern Theater Command	Tertiary, Guangzhou, Guangdong, China
Heyuan People’s Hospital	Medical Ethics Committee of Heyuan People’s Hospital	Tertiary, Heyuan, Guangdong, China

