#### Primary efficacy endpoint

The primary efficacy endpoint of this study is the proportion of patients with at least 1 VAP episode.

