#### Data analysis

All analyses will be performed according to the ITT principle. A *P* value < 0.05 is considered statistically significant. All tests are two-sided with no adjustment for multiple comparisons. Continuous variables are reported as means and standard deviations or medians and interquartile ranges. Categorical variables are reported as proportions. Pearson’s chi-squared test and adjusted multivariable analysis will be applied for the primary outcome. We plan to perform subgroup analyses for the primary outcome for predefined variables: the proportion of patients with at least 1 VAP episode. All the other data, including age, gender, body mass index (weight, height), SOFA score, primary admission diagnosis, coexisting illness, and type of admission, will be presented as descriptive results. Pearson’s chi-squared test will compare incidence or mortality outcomes between groups. The *t*-test will compare total VAP episodes, SOFA scores, time to VAP onset from mechanical ventilation, mechanical ventilation duration, ICU and hospital lengths of stay, inflammatory biomarkers, and function indicators between groups. A paired *t*-test or repeated measures ANOVA will be used to compare baseline and changes during the intervention.

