To address this call, the VIP study is a large-sample-sized, rigorous multicenter randomized trial that aims to determine whether PTF is effective and safe in preventing VAP. In ethical consideration to maximize patients’ benefit, bundling practices, including elevation of the head of the bed, daily sedation vacations, assessment of readiness to extubate, deep-vein thrombosis prophylaxis, and daily oral care, are also implemented by trained investigators according to the study protocol [56–59]. This strategy might result in a relatively lower occurrence of VAP in the control group, which in turn required larger sample size to detect the potential difference in VAP incidence between the intervention and control groups. Based on an elaborate sample size calculation, we aimed to enroll nearly 1,000 patients to powerfully detect the possible underlying profit of PTF over GTF in improving a range of clinical outcomes for ICU patients.

VIP study has several strengths. First, the RCT design can limit the risk of biases related to the presence of confounding factors in evaluating the preventive effects on VAP and mortality. Second, the VIP study includes representation of persons aged from 18 years to 80 years in different hospitals located all over China to enhance the generalizability of the findings. Third, we are also documenting baseline organ malfunctions with coexisting diseases and SOFA scores to understand further the relationship between body frailty and critical care-associated infections. Furthermore, to shorten the time from endotracheal intubation to PTF placement and limit the effects of management heterogeneity among centers on outcome variables, all tubes are placed using endoscopic methods by well-trained intensivists in the present trial.

In conclusion, the VIP study is a large-sample-sized, multicenter, open-label, randomized, parallel-group, controlled trial of PTF in China and is well-designed based on previous studies. The results of this trial may help provide evidence-based recommendations for the prevention of VAP.

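### The 924 patients and 80% power do not belong to the planned two-sided superiority test; 924 reproduces only for a one-sided 5% test against a 10-point margin that the analysis section does not contain

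*Protocol article*

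**What the plan says.** All statements are in the protocol article.

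- *Study design* describes a "GTF-controlled (PTF vs. GTF 1:1) superiority trial in 4 tertiary care hospitals".
- *Primary efficacy endpoint*: "The primary efficacy endpoint of this study is the proportion of patients with at least 1 VAP episode".
- *Sample size estimation* takes a control rate of 33.7% and a relative risk reduction (RRR) of 51.4%, allows 10% loss, and concludes: "We calculate that enrollment of 924 participants will have a power of 80% to detect an absolute reduction of 17.3" percentage points. The sentence before this one reads: "A 10% inferiority margin is predetermined following previous guidelines and reviews". The section gives neither a significance level nor sidedness, and does not say how the margin enters the calculation.
- *Data analysis* applies Pearson's chi-squared test and an adjusted multivariable analysis to the primary outcome. A *P* "value < 0.05 is considered statistically significant", and "All tests are two-sided with no adjustment for multiple comparisons". No margin appears there.
- *Discussion* says of the prevention bundle: "This strategy might result in a relatively lower occurrence of VAP in the control group". It adds that this calls for a larger sample, but gives no lower rate.

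**The concern.** A fall from 33.7% to 16.4% is a large effect for a binary endpoint, and a two-sided superiority test detects it with a few hundred patients at most. A total of 924 at 80% power suggests that a different test was sized. The margin sentence points the same way, because a margin plays no part in a test of zero difference.

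Two things are at stake. First, the stated power is not the power of the planned test, so the article does not tell its reader what 924 patients can detect. That matters because the Discussion expects the control rate to fall. Second, the hypothesis that appears to have set the size has a much stricter success threshold than the planned analysis. A moderate observed benefit would meet one and miss the other.

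**Working it through.** **Inputs.** Control rate p1 = 0.337, RRR 0.514, power 80%, loss 10%, margin 10 points (*Sample size estimation*); two-sided 0.05, chi-squared (*Data analysis*); 1:1 allocation (*Study design*). Reading the margin as 10 percentage points is an assumption, since its scale is not given.

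- p2 = 0.337 × (1 − 0.514) = 0.1638; d = 0.1732
- V = p1(1−p1) + p2(1−p2) = 0.2234 + 0.1370 = 0.3604
- Mean rate 0.2504, so 2 × 0.2504 × 0.7496 = 0.3754
- z = 1.960 (two-sided 5%), 1.645 (one-sided 5%), 0.842 (80% power)

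**1. Reproducing 924.** One-sided 5%, with the margin subtracted from the effect:

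n per arm = (1.645 + 0.842)² × V / (d − 0.10)² = 6.183 × 0.3604 / 0.0732² = 415.6, so 416

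Total 832; 832 / 0.9 = 924.4. This matches 924. With the rounded rate of 16.4% the same formula gives 419 per arm and 931.

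**2. The planned test (null difference zero, two-sided 5%).**

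n per arm = [1.960 × √0.3754 + 0.842 × √0.3604]² / 0.1732² = (1.2009 + 0.5052)² / 0.0300 = 97.0

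Rounded up to 98 per arm: 196 evaluable, 196 / 0.9 = 218. With a continuity correction: 109 per arm, 244 in total.

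**3. Power of the planned test at 416 per arm.** Standard error (SE) under the null √(0.3754/416) = 0.0300; under the alternative √(0.3604/416) = 0.0294.

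(0.1732 − 1.960 × 0.0300) / 0.0294 = 3.88, power 99.99%

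**4. The margin test at the stated two-sided 5%.**

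- 416 per arm: 0.0732 / 0.0294 − 1.960 = 0.53, power about 70%
- 462 per arm (all 924): SE 0.0279, 0.0732 / 0.0279 − 1.960 = 0.66, power about 75%
- Size for 80%: 7.849 × 0.3604 / 0.0732² = 527.6, so 528 per arm; 1,056 / 0.9 = 1,173.3, about 1,174

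**5. Other readings at the same rates.** A one-sided 5% test of zero difference needs 172 with loss. Non-inferiority with the assumed benefit needs 68 to 86; with equal rates, 616 to 780. None is near 924.

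**6. Success thresholds, 416 per arm, control rate 33.7%.** The chi-squared test reaches *P* < 0.05 from an observed reduction of about 6.3 points (33.7% to 27.4%). The one-sided margin test needs about 10 + 1.645 × 3.0 = 15 points.

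**7. What the planned test detects at 80% power** (step 2 formula solved for d):

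| Control rate | 832 evaluable | RRR |
|---|---|---|
| 33.7% | 8.8 points | 26% |
| 25% | 7.9 points | 32% |
| 20% | 7.2 points | 36% |
| 15% | 6.3 points | 42% |

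With all 924 analysed and a 33.7% control rate: 8.4 points (RRR 25%).

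**The case against.** The strongest reply is that no harm follows. The planned test keeps its type I error and has ample power for the stated effect, and the decision rule can be read from *Study design* and *Data analysis*: superiority, difference zero, two-sided 0.05. All of that stands. A reader might infer that the trial is underpowered, or that its success rule cannot be determined. The documents support neither. Power falls short only under a margin test that *Data analysis* does not plan.

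A second reply is that 924 was meant to cover the lower control rate foreseen in the Discussion. At the same RRR a control rate of 10% would need 907 patients with loss, so the size could be defended on that ground. But *Sample size estimation* fixes 33.7%, no lower rate enters it, and the margin formula gives 924 from its own figures.

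A third reply is that the one-sided level is reconstructed. That is correct: the 10% margin is stated, but the one-sided 5% and the subtraction are back-solved, and the exact match uses the unrounded 16.38%. The documents do not show that a one-sided test was planned. Nor is a margin out of place in every superiority trial, since superiority by a margin is a legitimate hypothesis. Here it is mislabelled, unexplained and not carried into the analysis.

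A reader might also take the Background to call the 51.4% effect implausibly large. It makes a general remark about meta-analyses of small trials and then says that the benefit may be underestimated, so it cannot be cited for that.

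**Conclusion.** The point holds as an inconsistency between the sample size statement and the planned analysis. The stated 80% is not the power of the stated test on either reading at two-sided 5%: it is above 99.9% without the margin and about 70% to 75% with it. The size is more than four times what the planned test needs for the stated effect (924 against 218). At a 33.7% control rate, an observed reduction between about 6.3 and 15 points would succeed under *Data analysis* but fail the hypothesis that reproduces 924.

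This rests on normal approximations, on the margin being 10 percentage points, and on 832 evaluable patients unless all 924 are named. That the one-sided margin test is the source of 924 is a well-fitting inference. The mismatch in steps 2 and 3 does not depend on it.

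**What to change.** Align *Sample size estimation* with *Study design* and *Data analysis*:

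- Remove the margin sentence and state a null difference of zero, two-sided 0.05.
- Keep 924 and restate what it gives at 80% power: about 8.8 points from 33.7% with 832 evaluable (RRR about 26%), or about 8.4 points with all 924 analysed. Both belong in the text, because the article follows withdrawn patients and analyses everyone randomised.
- Add the detectable reductions with 832 evaluable at control rates of 25%, 20% and 15%: about 7.9, 7.2 and 6.3 points.

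The cost is one reworded paragraph in an amendment, with no change in enrolment.

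If the sponsor does intend superiority by more than 10 points, write that null and its confidence-interval rule into *Data analysis*, and restate the power as about 70% (832 evaluable) to 75% (924) at two-sided 5%. Enrolment can stay at 924 if that power is accepted; 80% would need about 1,174 patients. The choice should be made and dated before outcome data by arm are seen.

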#### Analyses set

The study protocol mention that analysis will be done considering the “intention to treat” principle. However, some randomized patients did not allow feeding tube insertion (gastric or postpyloric) during study conduction due to illness severity, or the attending physician decided not to insert the tubes. Those cases are not excluded from the analyses. Patients who complete the randomization, regardless of whether they completed the trial or received the treatment in the designated group, are retained in the original group for analysis. The randomization information is maintained to the maximum extent.

#### Intention-to-treat set (ITTS)

ITTS refers to the ideal population of subjects meeting the ITT principles. To best retain the randomized information, ensure that the differences in trial results are attributed to the differences in treatment, and make the effect of treatment (postpyloric feeding) best assessed, the principle of ITT analysis is adopted. ITT set (ITTS) included all randomized patients, regardless of whether they have received nasogastric tube placement, completed the trial, or received the treatment of this group, all of whom remain in the original group for analysis.

#### Per protocol set (PPS)

PPS refers to all participants who fulfill the eligibility criteria and achieve gastric or postpyloric tube placement per randomization. They have good compliance with the trial protocol, such as being ready to receive treatment and measurement for the primary efficacy endpoints, with the required contents in the CRF filled. PPS is used to analyze the primary efficacy endpoints.

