### Data management

Trained staff will perform data management at each center using the Electronic Data Capture (EDC) system (https://www.mmphcrc.com/pdf/medicalHistory/vapcrf.html). The EDC system’s reliability, access control, and traceability will guarantee the quality of trial data management. Data collection will be restricted to those variables necessary to define baseline patient characteristics (demographics, VAP diagnosis, concurrent medical conditions and comorbidities, inclusion and exclusion criteria, severity of illness and organ dysfunction scores, vital signs, and laboratory results), the delivery of the nutrients, potential confounding co-interventions (life-sustaining therapies, and use of vasopressors or sedatives), and outcomes (vital signs at ICU and hospital discharge, day 28, length of stay in ICU and hospital). Randomized participants will be followed until either death or 28 days after randomization, whichever comes first. Study staff will attend follow-up by either direct contact with the patient or the next of kin. Participants who withdraw from the study will be followed up according to the follow-up schedule and analyzed on the ITT principle.

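### The per-protocol section assigns the primary endpoint to the per-protocol set without qualification, while the rest of the protocol applies intention to treat and never says the per-protocol result is only supportive

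*Protocol article*

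**What the plan says.** The design is a "GTF-controlled (PTF vs. GTF 1:1) superiority trial in 4 tertiary care hospitals" (Study design). Under Primary efficacy endpoint: "The primary efficacy endpoint of this study is the proportion of patients with at least 1 VAP episode".

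Four sections point to ITT:

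- **Analyses set.** Some randomised patients had no feeding tube inserted, gastric or postpyloric, because of illness severity or the attending physician's decision. Of them it says: "Those cases are not excluded from the analyses".
- **Intention-to-treat set.** "ITT set (ITTS) included all randomized patients, regardless of whether they have received nasogastric tube placement, completed the trial".
- **Data management.** "Participants who withdraw from the study will be followed up according to the follow-up schedule and analyzed on the ITT principle".
- **Data analysis.** "All analyses will be performed according to the ITT principle".

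One section points elsewhere. The per-protocol section restricts the PPS to eligible participants who "achieve gastric or postpyloric tube placement per randomization", who comply well with the protocol and whose required case report form contents are filled in. It closes with "PPS is used to analyze the primary efficacy endpoints".

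**The concern.** The patients whom the Analyses set section insists on keeping are the ones whom the PPS definition removes, and the PPS is the only set definition that names the primary efficacy endpoints. A reader of the published protocol could defend either set as the one specified for the primary result. The choice matters because the conclusion of a superiority trial should rest on the groups as randomised.

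PPS membership depends on what happens after randomisation: whether the tube was placed, how compliance was judged and whether the form was complete. By the protocol's own account, non-placement is partly a matter of illness severity and partly a clinician's decision, and the trial is open-label. If these exclusions differ between arms in number or in prognosis, the PPS comparison is no longer protected by randomisation.

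**Working it through.** **1. The text side by side.** The conflict needs no arithmetic.

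| Section | Patient with no tube placed | Role given to the set |
|---|---|---|
| Analyses set | kept | general principle |
| Intention-to-treat set | kept, original group | principle adopted, no endpoint named |
| Data analysis | kept (ITT) | all analyses |
| Data management | does not address tube placement; withdrawals followed and analysed by ITT | general |
| Per protocol set | removed | primary efficacy endpoints |

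No section calls the PPS secondary, supportive or a sensitivity analysis, and none says which result prevails.

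**2. Sample size.** The analysis set does not enter the calculation of 924. That figure comes back with 33.7% against 33.7% × (1 − 0.514) = 16.4%, the stated 10-point margin, one-sided 0.05 and 80% power:

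n per arm = (0.337 × 0.663 + 0.1638 × 0.8362) × (1.645 + 0.842)² / (0.1732 − 0.10)² ≈ 416

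The total is 832, and 832 / 0.9 = 924.4. Naming ITT as primary changes none of these inputs.

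**3. What PPS exclusions could do.** From the protocol: 33.7% VAP, 924 / 2 = 462 per arm, two-sided 0.05, Pearson chi-squared test. Assumed, and not in the documents: no true effect, the fraction f excluded, and the VAP risk r in those excluded.

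- Rate left in an arm after exclusion: q = (0.337 − f × r) / (1 − f). Where the risk is given as k times that of placed patients: q = 0.337 / (k × f + 1 − f).
- Spurious difference: d = control rate − q.
- Rejection probability: Φ((d − 1.96 SE₀)/SE₁) + Φ((−d − 1.96 SE₀)/SE₁), with SE₀ pooled, SE₁ unpooled, and n = 462(1 − f) in an arm with exclusions.

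Worked case, f = 0.10 and r = 0.60 in the postpyloric arm only: q = (0.337 − 0.060)/0.90 = 0.3078; d = 0.0292; n = 462 and 415.8; SE₀ ≈ SE₁ ≈ 0.0316; (0.0292 − 0.0619)/0.0316 ≈ −1.04, giving 0.150. The other tail adds 0.002, so the total is 15.2%.

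| Assumed exclusions | Spurious benefit of postpyloric feeding (points) | Two-sided type I error |
|---|---|---|
| Equal fraction and risk in both arms | 0 | 5.0% |
| 2% postpyloric only, 1.25 times the risk | 0.2 | 5.0% |
| 5% postpyloric only, 50% to 60% risk | 0.9 to 1.4 | 5.9% to 7.3% |
| 10% postpyloric and 5% gastric, 55% risk | 1.2 | 6.8% |
| 10% postpyloric only, 50% to 60% risk | 1.8 to 2.9 | 8.8% to 15.2% |
| 15% postpyloric only, 50% to 60% risk | 2.9 to 4.6 | 14.5% to 30.6% |

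The sign can change. If 10% of the postpyloric arm is excluded at an observed risk of 20%, q = (0.337 − 0.020)/0.90 = 0.352. The spurious difference is then 1.5 points against postpyloric feeding.

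**The case against.** The strongest reply is that this is an ordinary arrangement of ITT plus a per-protocol analysis with one label missing. Four sections favour ITT, and the intention-to-treat section adopts the principle expressly so that the effect of postpyloric feeding is best assessed. The per-protocol sentence does not say that the PPS replaces ITT or that it is the primary analysis. Nor can the statement that all analyses follow ITT be fully literal, because the safety section uses its own set as the denominator for adverse events. There may therefore be room for a supportive PPS. Ranking of analysis sets is also often left to a statistical analysis plan.

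Much of this stands. A reader might infer that the protocol makes the PPS its primary analysis, or sets up two equal primary analyses, and the weight of the text is against that. It does not dispose of the point, because the article does not leave the matter open: it states two rules that conflict, one of them unqualified.

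A reader might also infer that the PPS drops only failed postpyloric placements and so must favour that arm. The documents do not support this. The PPS rule covers gastric and postpyloric placement alike, and no failure rate is given for either tube. More non-placement in the postpyloric arm is plausible: the section on endoscopic placement describes endoscopy under sedation for that arm and a nurse-inserted tube for controls. But the same section says endoscopy was chosen for prompt and reliable placement and that training is provided, and patients with contraindications to tube placement are excluded. The excluded patients might also show less VAP, if they die or are extubated before it can occur.

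**Conclusion.** The point holds as a contradiction in the text. The PPS is named for the primary endpoint without qualification, against ITT statements elsewhere, and nothing makes the PPS result supportive. This conclusion rests on wording alone.

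The statistical consequence is conditional. It arises only if the PPS result were treated as decisive, and its size depends on assumptions about exclusions that the documents do not inform. Under no true effect, type I error would stay at about 5% with few or balanced exclusions, and be about 6% to 7% if 5% of the postpyloric arm were lost at 50% to 60% risk. It would be about 9% to 15% if 10% were lost at those risks, and about 31% at the far end examined. Bias towards postpyloric feeding needs both more non-placement in that arm and a higher VAP risk in those patients; a lower observed risk would reverse it. The documents do not show that inflation of 9% or more is to be expected.

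**What to change.** Replace the last sentence of the per-protocol section with: *The primary analysis of the primary endpoint is in the ITT set and alone determines the trial's conclusion; the PPS analysis of the primary endpoint is a supportive sensitivity analysis.*

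Change the opening sentence of Data analysis to: *All efficacy analyses will be performed according to the ITT principle, with the PPS as a sensitivity analysis and the safety set for adverse events.*

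The cost is two sentences, best recorded as a dated amendment before any comparison by arm is made. The sample size, data collection and conduct of the trial do not change.
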